#### Secondary analyses

Multilevel mediation analyses will be conducted to evaluate the possible underlying mechanisms of action in MBCP. In these analyses only participants considered to be “treated” i.e., those who have received at least five out of nine MBCP sessions will be included. We will examine the mediating effect of general mindful awareness, self-compassion, and catastrophic beliefs.

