### Aims

The ‘I’ve Changed My Mind study’ is designed with four primary aims: 1) to assess the effects of MBCP, as compared to FoCC, on the primary outcome measures of a) FoC, b) labour pain, and c) willingness to accept obstetrical interventions without medical indications in pregnant women with a high level of FoC; 2) to assess the effects of MBCP, as compared to FoCC, on the secondary outcome measures of a) anxiety, b) depression, c) general stress, d) pre- and postnatal stress, e) quality of life, f) sleep quality of women, her partner and infant, g) pre- and postnatal fatigue, h) satisfaction with childbirth, i) birth outcome for mother and child, and j) breastfeeding self-efficacy in pregnant women with a high level of FoC and their partners; 3) to examine overall mindful awareness, self-compassion, and catastrophic beliefs as possible mediating mechanisms underlying the effectiveness of MBCP; 4) to assess the costs of health care use due to FoC and cost-effectiveness of MBCP as compared to FoCC. These four aims will be examined in three time periods: a) during pregnancy, b) after labour, and c) during the maternity leave period following the birth.

It is hypothesized that participants in the MBCP group, as compared to those in the FoCC group will a) show larger and longer lasting effects on all primary and secondary outcome measures, b) demonstrate increased overall mindful awareness and self-compassion, and decreased catastrophic beliefs, and c) have lower FoC related health care costs, indicating that MBCP is more cost-effective than FoCC.

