### Active Comparison Condition: Fear of Childbirth Consultation (FoCC)

The target sample of pregnant women included in this study suffer from intense FoC. In order to acknowledge the fears of these women we have upgraded care as usual into structured consultations on FoC (FoCC). FoCC consists of an adaptation of the Biopsychosocial Model [5] and the Childbirth Plan of the Royal Dutch Organization of Midwives (KNOV) [59].

This individualized programme for expectant couples includes two consultation sessions with a trained midwife of one-hour each over a nine-week period (see Table 3). The aim of FoCC is to gain insight into the variety of specific factors playing a role in the origin and presence of fear and stress around pregnancy, birth and the postpartum period as well as designing a suitable coping plan based on the particular fears and stresses, and includes some components of psychoeducation about fear. A structured form is used to collect information about FoC related factors and for the coping plan. The coping plan may include referral to a psychologist or other mental health care services. All FoCC sessions will be audio recorded in order to assure treatment fidelity. Two recordings per consultation will be randomly selected and evaluated by an independent midwife. The free of charge FoCC sessions will take place at the participant’s midwifery practice or place of residence.

**Table 3 Tab3:** Outline of the Two Sessions of the Fear of Childbirth Consultations

FoCC First Consultation
Mapping of the bodily, mental and social factors underlying FoC and the postpartum period. Interview about the pregnant woman’s overall state of physical health and current pregnancy, her mental health and emotional state, her ideas and values regarding being pregnant, the process of giving birth and being a parent, incidence of psychopathology in her family of origin, her most severe fears about childbirth and the postpartum period, her relationship with her partner, family, presence of social support, workplace experiences, important life events and potential vulnerabilities. A written psychoeducation about FoC and matching behavior from a body and mind perspective is provided.
FoCC Second Consultation

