### Primary outcome measures

Primary outcome measures are (a) FoC, (b) labour pain, and (c) willingness to accept obstetrical interventions without medical indications.

The complexity of FoC will be measured by three instruments, namely the W-DEQ- A and B [3], the newly developed Perinatal Disaster Scenarios Scale (PDSS), ([name], [name], [name], [name]: PDSS, unpublished), and the experimental Perinatal Anxiety/Fear Scale (PAFS), ([name], [name], [name]: PAFS, unpublished). First, anticipated and experienced levels of FoC will be assessed with the 33 items self-report W-DEQ- A and B covering several domains of FoC: (a) general fear, (b) negative appraisal, (c) loneliness, (d) lack of self-efficacy, (e) lack of positive anticipation, and (f) concerns about the child [61]. Second, the individual perinatal fear-eliciting beliefs, in pregnant women and their partners, will be assessed by the PDSS. We developed the PDSS, which is based on the Social Phobia Belief Scale (SPBS) [62], for this study in order to describe catastrophic beliefs about childbirth and future-related events that are eliciting fear (maximum of 3 beliefs). The PDSS assesses the probability of actual occurrence of those catastrophic events, the severity, and the ability to cope with them in the future on the Visual Analogue Scale (VAS) [63], (0–100 %). And third, to assess responses to anxiety and fear in pregnant women we will administer the experimental PAFS based on the Dimensional Anxiety Self-report of Social Phobia level 3 DSM-IV [64].

Subsequently, three instruments will be included to assess labour pain. First, anticipated and experienced cognitive and emotional components of labour pain will be assessed by the 13 item self-report Catastrophizing Labour Pain (CLP) subscale derived from the Labour Pain Cognitions and Coping List (LPCCL) [65], the 20 item self-report Labour Pain Acceptance Questionnaire (LPAQ), ([name], [name], [name], [name], [name]: LPAQ, unpublished), an adaptation of the Chronic Pain Acceptance Questionnaire (CPAQ) [66], and the expected and experienced severity of labour pain will be assessed by the VAS [63] (0–10).

Last, the willingness to accept obstetrical interventions without medical indications will be assessed by the Dutch version of the Willingness to Accept Obstetrical Interventions measure (WAIO) [67], ([name], [name], [name], [name]: Dutch version of WAIO, unpublished).

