### Mechanisms of action and process evaluation

Changes in overall mindful awareness, self-compassion, and catastrophic beliefs are hypothesised to be potential underlying working mechanisms of MBCP leading to positive changes in mental health and behaviour during the perinatal period. Overall mindful awareness including qualities such as observing, describing, acting with awareness, non-judging and non-reactivity to inner experience, will be assessed by the Five Facet Mindfulness Questionnaire (FFMQ) [81]. In addition, mindful awareness specifically related to one’s role as a (new) parent will be assessed with the Interpersonal Mindfulness in Parenting Scale (IM-P) [82]. Self-compassion will be assessed by the Self-Compassion Scale-Short Form (SCS- SF) [83], and catastrophic beliefs will be assessed by the Perinatal Disaster Scenarios Scale (PDSS).

Expectancy effects in women and partners will be assessed by the question: “If you had a choice, which one of the study’s programmes would you prefer to participate in?”. Adherence to MBCP will be assessed by number of classes attended and weekly diaries of the number of minutes spent in formal meditation practice each week between sessions. Data regarding the number of attended sessions of FoCC will also be collected.

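### The mediation set is defined by MBCP attendance alone, so the test of mechanism has no sound MBCP-versus-FoCC comparison

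*Protocol article*

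**What the plan says.** The Secondary analyses section of the protocol article plans multilevel mediation analyses and sets their population: "In these analyses only participants considered to be “treated", defined as "those who have received at least five out of nine MBCP sessions will be included". It names the mediators: "We will examine the mediating effect of general mindful awareness, self-compassion, and catastrophic beliefs". It gives no criterion under which a FoCC participant enters.

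The comparison condition "includes two consultation sessions with a trained midwife of one-hour each over a nine-week period" and contains no MBCP session. The section on mechanisms of action says FoCC attendance will be recorded, but the definition of the mediation set does not use it.

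Aim 3, one of four aims listed as primary, covers mindful awareness, self-compassion and "catastrophic beliefs as possible mediating mechanisms underlying the effectiveness of MBCP". The hypothesis about these mediators in the same section is worded as MBCP against the FoCC group.

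The Primary analyses section, by contrast, plans an intention-to-treat model in both conditions with a time-by-condition interaction.

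On the instruments, "catastrophic beliefs will be assessed by the Perinatal Disaster Scenarios Scale (PDSS"), while the Primary outcome measures section states that "The complexity of FoC will be measured by three instruments", of which the PDSS is one.

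**The concern.** In a two-arm trial, mediation asks whether allocation shifts the mediator and whether that shift carries part of the effect on the outcome. The first link needs both arms. A set that only MBCP attenders can enter has no comparison arm, and FoCC is what separates an MBCP-specific change from change that would have occurred anyway. All women enter with W-DEQ-A of 66 or more, and all move through late pregnancy and birth during follow-up. Before-and-after change in adherent women therefore cannot by itself be credited to MBCP.

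At stake is the answer to aim 3. A report could name mindful awareness or self-compassion as the mechanism of MBCP when the data cannot show that MBCP moved it more than FoCC did.

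This is a rule the article states, not a detail it leaves to an analysis plan that is not shown.

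**Working it through.** **1. The plan's own figure.** The plan gives no number for the mediation analysis. Its only related figure is 128 women (64 per arm) for the primary interaction. Taking medium as d = 0.5 (assumed; no number is given), two-sided 5% and 80% power: n per arm = 2 × (1.960 + 0.842)² / 0.5² = 62.8, so 63. The exact t-test gives 63.8, so 64, with power 0.801. With correlation 0.5 the SD of change is √(2 × (1 − 0.5)) = 1, so the T1–T2 interaction needs the same number. The figure reproduces and is not in dispute.

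**2. Literal reading.** Let C = 1 for MBCP and 0 for FoCC, and let the mediator model be M = α + a·C + error. FoCC women attend no MBCP sessions, so none meets the five-session rule, and C = 1 for everyone kept. The variance of C is 0, the columns for intercept and condition are identical, and the design matrix has rank 1 of 2. The path a cannot be estimated, so neither can the indirect effect a × b of MBCP versus FoCC. What remains is change over time and mediator–outcome association within one arm.

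**3. Lenient reading (MBCP attenders against all FoCC women).** Suppose MBCP has no effect on mediator or outcome. Assume one prognostic factor U correlates 0.5 with each of them and 1/√2 ≈ 0.707 with the propensity to attend, with higher values favourable throughout. If a share p attends at least five sessions, the false difference on either variable is 0.5 × 0.707 × φ(z_p)/p, where φ is the normal density and z_p the normal quantile of p. A simulation of 2,000,000 records agrees:

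| Share attending p | φ(z_p)/p | Formula (SD) | Simulated, mediator (SD) | Simulated, outcome (SD) | Mediator–outcome slope in attenders |
|---|---|---|---|---|---|
| 60% | 0.644 | 0.228 | 0.231 | 0.226 | 0.190 |
| 70% | 0.497 | 0.176 | 0.179 | 0.175 | 0.197 |
| 80% | 0.350 | 0.124 | 0.126 | 0.123 | 0.208 |
| 90% | 0.195 | 0.069 | 0.072 | 0.068 | 0.220 |

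The slope is also false, because it comes only from U. In unselected women it is 0.5 × 0.5 = 0.25. The false indirect effect is the mediator difference times a slope between the attender value and 0.25: from 0.231 × 0.190 = 0.044 to 0.231 × 0.25 = 0.058 SD at 60% attendance, and from 0.072 × 0.220 = 0.016 to 0.072 × 0.25 = 0.018 SD at 90%. The true value is 0.

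**4. Both arms as allocated, same assumptions.** U is then balanced between arms if the arms are comparable at entry, so a = 0. The false slope of 0.25 is still there, but a × b = 0 × 0.25 = 0. Keeping everyone removes the false indirect effect in this setting. It does not remove confounding of the mediator–outcome path in general.

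**5. The PDSS.** If the same PDSS score at the same wave were both mediator and outcome, the relation would be an identity. PDSS to W-DEQ is not of this kind, and neither is any path from the FFMQ or SCS-SF.

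**The case against.** The best defence is that the analysis was meant to look inside MBCP. Aim 3 and the Secondary analyses section speak of mechanisms of MBCP and do not repeat the comparison with FoCC that aims 1, 2 and 4 make. A multilevel mediation with time as predictor can be estimated in one arm, and the comparative hypothesis on mediator levels can be tested outside the mediation set. This stands in part: a reader might infer that nothing can be estimated, and that is too strong. But effectiveness in this trial means effectiveness against FoCC, and one-arm change is uncontrolled evidence for a mechanism behind it.

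A second defence is that the threshold was obviously meant for the MBCP arm. The text does not say so, and that reading brings in the selection shown in step 3 of the working.

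Several stronger readings are tempting but not supported:

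- **The PDSS explains itself.** No outcome is named for the mediation models, and the three FoC instruments are listed without a composite. Circularity arises only if the PDSS is made the outcome where it is the mediator.
- **Mediator and outcome have no time order.** No same-visit path is stated. Table 4 schedules the FFMQ, SCS-SF and PDSS at T1 to T4 and the W-DEQ-B at T3 and T4, so lagged models are possible.
- **A fixed share of the sample is lost.** The Recruitment section continues until at least 64 women per arm have completed their programme, so 64 may count completers rather than women allocated.
- **Regression to the mean alone yields mediation.** Women are selected on W-DEQ-A, not on the FFMQ or SCS-SF. A false indirect path needs the mediator to move as well.

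**Conclusion.** The concern holds for the attendance rule. As written, the mediation set contains no FoCC women, and the MBCP-versus-FoCC indirect effect is not estimable. That conclusion needs no numerical assumption beyond FoCC women receiving no MBCP sessions. Under the lenient reading the comparison is biased by self-selection whenever attendance is related to prognosis. In the illustration the false difference is about 0.07 to 0.23 SD on mediator and outcome, and the false indirect effect about 0.02 to 0.06 SD. Those sizes depend on the assumed correlations and on attendance between 60% and 90%, none of which the protocol gives.

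The PDSS overlap is a conditional note about one of three mediators.

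A reader might infer that the trial's main result is compromised. It is not: the primary analysis is intention-to-treat in both conditions, and the sample size does not depend on the mediation set. The point should be fixed because aim 3 is listed as primary, but it is not critical to the main comparison.

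**What to change.** Define the mediation population as all allocated women of both arms, analysed as allocated, with condition as the exposure, in line with the approach in the Primary analyses section. Keep the five-session set as a sensitivity analysis only, state whether FoCC women are in it, and describe it as an attendance-selected comparison. Add one sentence that the PDSS will not be the outcome in any model where it is the mediator; it may still serve as mediator for the W-DEQ.

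The cost is a change of wording. Table 4 already schedules the FFMQ, SCS-SF, PDSS and W-DEQ, so no new measurement or recruitment is needed. Allocation is by alternation and the Discussion accepts a risk of bias from it, so even the corrected analysis should be reported with that caution.

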### Statistical analyses

#### Primary analyses

Dichotomous outcome data will be analysed using Chi-square tests or logistic regression using the method of ‘last observation carried forward’ (i.e., assuming no change) to handle dichotomous incomplete data. Continuous outcome data will be analysed with Multi-level analyses. Multi-level analyses with full information maximum likelihood (FIML) estimation use all available data and allow intention-to-treat analyses including all participants with incomplete data and participants who dropped out during the study. Continuous variables will be transformed into *Z*-scores. In this way, the parameter estimates can be interpreted as a measure of effect: i.e., as Cohen’s *d* for dichotomous predictors and as *r* for continuous predictors. Outliers will be identified. Analyses will be run twice: once in which all original scores will be included and once in which outliers will be changed to *Z*-scores (-) 3.29. Dependent variables will be level of FoC, labour pain and willingness to accept obstetrical interventions without medical indications. Predictors will be the different time measurements (T2, T3, and T4 against T1) and condition (MBCP versus FoCC). Interaction effects of time X condition will be added to the model to examine which programme is more effective over time.

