Some limitations to this study design need to be considered. First, the quasi-experimental study design creates less homogeneous groups then with full randomization (RCT) and permits a greater risk of bias due to potential alternation and allocation problems. To work with this, we adopted the recommendations for designing the Q-RCT studies from the Cochrane Handbook for Systematic Reviews of Interventions [86]. Due to the steadily increasing gestational age, dependency on recruitment speed and efficiency, and the required size of approximately six participants in the intervention group, we are obliged to use the quasi-randomization procedure in order to be able to conduct this study efficiently. A second limitation is the uncertainty of the power of this study due to the unknown effect size of the comparison group. To cover this limitation, we have chosen to downsize the expected large effect size of MBCP as shown in Duncan and [name]’s [40] study to a medium effect size in order to not under-power our study. An additional limitation is the potentially sizable dropout of participants due to their possibly strong preferences for one of the study’s interventions, the nine weeks duration of the programmes, and the relatively long and direct follow up after the birth. As a retention strategy we provide the participants with a financial incentive (€50) for completing the measurements following the birth.

Among the strengths of this study are the clinical-based experimental design, the extensive cognitive-emotional and behavioural measurements in pregnant women and their partners during the entire perinatal period, and the representativeness of the study sample as well as the generalizability of the study’s results. The complex and innovative measurements of FoC in this study are an important strength in research on FoC not only in pregnant women but also in their partners.

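### The mediation analysis for Aim 3 is limited to participants with at least five of nine MBCP sessions, a rule no FoCC participant can meet, so the allocated comparison is lost.

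*Protocol article*

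**What the plan says.** Aim 3, one of four aims that the article calls primary, is to examine mindful awareness, self-compassion and catastrophic beliefs as "possible mediating mechanisms underlying the effectiveness of MBCP". The matching hypothesis in the same section is a between-arm one: compared with FoCC, MBCP participants will "demonstrate increased overall mindful awareness and self-compassion, and decreased catastrophic beliefs".

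The analysis for this aim is under Secondary analyses: "Multilevel mediation analyses will be conducted to evaluate the possible underlying mechanisms of action in MBCP". Its analysis set is the participants regarded as treated, namely "those who have received at least five out of nine MBCP sessions will be included".

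The comparison arm receives "two consultation sessions with a trained midwife of one-hour each over a nine-week period" and no MBCP classes. Its attendance is recorded (Mechanisms of action and process evaluation: "Data regarding the number of attended sessions of FoCC will also be collected"), but no attendance threshold is attached to it.

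For continuous outcomes, Primary analyses describes likelihood-based multilevel models that "allow intention-to-treat analyses including all participants with incomplete data and participants who dropped out during the study". That statement is not carried over to the mediation models, and no mediation analysis of all allocated participants is given.

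**The concern.** The hypothesis about the mediators compares two allocated arms, but the analysis set is defined by something that happens after allocation in one arm only. The text can be read in two ways.

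- **Literal.** Only people with five MBCP sessions enter, so there are no FoCC participants. Condition does not vary, and the model describes change within MBCP. Fear, mindfulness and catastrophic beliefs may change as pregnancy advances, and nothing in the model separates that from the programme.
- **Loose.** The rule trims the MBCP arm and FoCC enters whole, including any FoCC participants who attended neither consultation. Selected attenders are then compared with an unselected group.

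The loose reading does harm only if attendance is related to response. The article itself makes that plausible: the Discussion expects "potentially sizable dropout of participants due to their possibly strong preferences for one of the study’s interventions", and also names the length of the programmes. That sentence concerns dropout, but low attendance is a likely expression of the same preferences. If those who attend would have changed more anyway, the path from condition to mediator is shifted and an indirect effect can appear where there is none. At stake is the answer to Aim 3.

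**Working it through.** **The plan's own figure.** The article gives 64 per arm for 80% power at 5% alpha with a medium effect. Taking medium as a standardised difference of 0.5 (assumed; no number is given), a two-sample t-test needs 63.8 per arm, and 64 per arm gives a power of 0.801. The figure reproduces. Here it only supplies the 64 per arm used below.

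**Can FoCC meet the rule?** The rule requires at least 5 MBCP sessions. FoCC offers 2 consultations and 0 MBCP sessions, so no FoCC participant qualifies. This step needs no assumption.

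**Literal reading.** Assume 75% of the MBCP arm reaches five sessions: 0.75 × 64 = 48. Suppose the mediator changes by 0.3 SD for reasons unrelated to MBCP. For a one-sample t-test of change, the noncentrality is 0.3 × √48 = 2.08, against a two-sided critical value of about 2.01 on 47 degrees of freedom. The power, here the chance of a spurious finding, is 0.53.

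That is the change test alone. A simulation that also required a significant mediator–outcome path (correlation 0.5, 80% attendance) declared mediation in 27%, 54% and 91% of trials for natural changes of 0.2, 0.3 and 0.5 SD, and in 4.7% with no natural change.

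**Loose reading.** Inputs: 64 allocated per arm (article). Assumed: no true MBCP effect, mediator–outcome correlation 0.5, a share *p* of the MBCP arm reaching five sessions, and a correlation *r* between the tendency to attend and mediator change. The expected shift in the mediator path is

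shift = *r* × φ(*z*) / *p*, with *z* the normal quantile of *p*.

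The factor φ(*z*)/*p* is 0.195 at 90%, 0.424 at 75% and 0.644 at 60%. Mediation is declared when both paths have p < 0.05 (4000 simulated trials per setting).

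| Analysis set | *r* | Shift (SD) | False mediation |
|---|---|---|---|
| All allocated, both arms | – | 0 | about 5% |
| Attenders v all FoCC, 50% to 90% attend | 0 | 0 | about 5% |
| 90% attend | 0.3 | 0.195 × 0.3 = 0.058 | about 6% |
| 75% attend | 0.3 | 0.424 × 0.3 = 0.127 | about 10% |
| 75% attend | 0.4 | 0.424 × 0.4 = 0.169 | about 14% |
| 60% attend | 0.3 | 0.644 × 0.3 = 0.193 | about 15% |
| 60% attend | 0.4 | 0.644 × 0.4 = 0.258 | about 24% |

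Simulation error is under one percentage point: at 24%, √(0.24 × 0.76 / 4000) = 0.7 points. Whether attendance is linked to the outcome only through the mediator or to both makes no material difference. Over a wider grid (50% to 90% attendance, *r* from 0 to 0.5) the rate runs from about 5% to 46%.

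**The case against.** The best defence is that this is an explanatory analysis under a secondary heading. It asks how the programme works in those who received it, which is a legitimate question. The comparison of MBCP with FoCC on continuous outcomes includes everyone and is untouched. This stands, and it limits the severity. It does not rescue the rule, because the attender-only analysis is the only one stated for an aim listed among the primary ones, and the hypothesis is framed against FoCC.

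A second objection is that the size of the bias rests on assumed inputs. That also stands for the loose reading. A reader might infer that the analysis will produce a false mechanism, but the documents do not support that: with high attendance, or attendance unrelated to response, the distortion is negligible. The loss of the comparison arm under the literal reading does not depend on those inputs, although the 53% figure depends on the assumed 48 participants and 0.3 SD change.

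A reader might also infer that discarding low attenders costs power: for a 0.5 SD mediator effect, 80% with 64 v 64 falls to 74% with 48 v 64 or 68% with 38 v 64. The documents do not support this either. The Recruitment section says recruitment goes on until at least 64 participants per arm have completed the programme. Completion is undefined, and if it means five or more sessions, about 64 attenders remain. The comparison also holds the effect at 0.5 SD in both sets. If non-attenders gain nothing, the effect in all allocated participants is 0.75 × 0.5 = 0.375 SD or 0.60 × 0.5 = 0.30 SD, with power of 56% or 39%, so the direction reverses.

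Using allocation as an instrument for attending five sessions may look like a natural remedy. It would require that one to four classes do nothing and that allocation acts only through attendance. Both are doubtful in a graded programme with an active comparator, and a complier effect of attendance is not an indirect effect through mindfulness.

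**Conclusion.** The concern holds as a fault in how the analysis set for Aim 3 is fixed. On either reading, the stated rule breaks the allocated comparison in which the mediator hypothesis is framed. On the literal reading, there is no comparison arm at all. On the loose reading, the harm ranges from nil to substantial, with false mediation of about 5% to 24% over the attendance shares of 60% to 90% and correlations of 0 to 0.4 tabulated. Those values are assumptions, because the article gives neither attendance nor its link to response.

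This should be fixed, but it does not threaten the trial's main result. The conclusion affected is the one about mechanism.

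**What to change.** Reword Secondary analyses so that:

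- the main mediation analysis includes all allocated participants in both arms, meaning women, and partners where they complete the mediator scales (Table 4 marks the FFMQ, SCS-SF and PDSS as completed by both);
- allocation (MBCP v FoCC) is the exposure, with the same likelihood handling of missing data as in Primary analyses;
- the five-of-nine set is kept only as a labelled supportive analysis, with a statement of how FoCC participants enter it.

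No new data are needed. The cost is that non-attenders dilute the indirect effect, so power for it may be lower. Analysing everyone removes the selection on attendance but not confounding between mediator and outcome, which remains on any analysis set and should be acknowledged when the results are interpreted.
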